### Harms

2.7

Given the non-invasive nature of the intervention, no serious adverse events are anticipated. An adverse event is defined as any unintended negative psychological or physical experience reported by a participant during or following a session, including clinically significant increases in anxiety or acute emotional distress. Adverse events will be monitored by the delivering midwife at each session using the standardised session log and reported to the principal investigator within 24 h. Participants experiencing clinically significant deterioration will be referred to appropriate services in accordance with the safety protocol described in section Criteria for Discontinuing or Modifying the Intervention.

In cases where a participant develops severe anxiety, acute distress, or suicidal ideation, the delivering midwife will immediately notify the principal investigator, discontinue participation, and refer the participant to specialist psychiatric services. All such events will be reported to the Bioethics Committee of the Medical University of Gdańsk.

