### Objectives

1.2

The primary objective of this study is to evaluate whether a tailored, individualised psychoeducational programme delivered by a trained midwife during the second and third trimester reduces the levels of PrA in low obstetric-risk Polish women, as measured by the PRAQ-R2 at 34–37 weeks of gestation.

The specific objectives are:

To evaluate the effect of the intervention on the levels of pregnancy-related anxiety at 34–37 weeks of gestation and at six or more weeks postpartum.To determine whether a reduction in PrA is associated with improved birth outcomes, including mode of birth and rates of elective caesarean section without medical indication.To assess the effect of the intervention on childbirth satisfaction and postpartum psychological wellbeing.To monitor and report any unintended adverse effects of the intervention, including temporary increases in emotional distress during or following sessions.

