#### Control group

2.5.1

Women in the control group will receive standard antenatal care as is typical in Poland, comprising: antenatal education in accordance with the Polish Organizational Standard of Perinatal Care (46), covering pregnancy, childbirth, puerperium and social support; routine obstetric appointments and ultrasound examinations; and hospital care during and after childbirth provided by designated hospital staff. In addition, women in the control group will receive an informational booklet on preparing for childbirth, developed specifically for this trial by midwives from the research team. The booklet covers key topics including the physiology of labour and birth, pain management options, hospital admission procedures, postpartum care, and newborn care. It is designed to provide factual information without therapeutic or psychoeducational components, thereby serving as a minimal active control condition that addresses ethical concerns while maintaining a meaningful contrast with the intervention.

Although standard antenatal education in Poland covers some overlapping topics (e.g., childbirth physiology), it is delivered in a group format without individualised psychological assessment or anxiety-focused components. The intervention differs fundamentally in being individually tailored to each participant’s anxiety profile and grounded in a structured therapeutic framework. To monitor the integrity of the control condition, participants will be asked at each follow-up assessment to report the content and format of antenatal education received; this information will be recorded and included as a covariate in sensitivity analyses if meaningful variability is identified.

Potential contamination between groups is addressed in detail in the Concomitant Care section, including measures to minimise cross-group communication and a planned sensitivity analysis.

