### Participant timeline

2.8

The schedule of enrolment, interventions, and assessments is presented in Figure 1 and Table 2. Eligible participants will be enrolled and randomised between 24 and 30 weeks of gestation (Time I). The intervention will be delivered between 24 and 34 weeks of gestation. The primary outcome assessment will be conducted at 34–37 weeks of gestation (Time II). The postpartum assessment will be conducted at six or more weeks after delivery (Time III). The duration of recruitment will continue until the target sample size of 37 participants per group is achieved.

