
#### Time II—post-intervention assessment

2.12.2

The second phase of data collection will consist solely of a follow-up measurement using the PRAQ-R2 to assess changes in the primary outcome.

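### Adverse-event collection is one-sided and tied to intervention sessions, so the fourth specific objective can be met only descriptively and incompletely

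*Protocol article*

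**What the plan says.** The Harms section (2.7) defines an adverse event as "any unintended negative psychological or physical experience reported by a participant during or following a session". It names one way of collecting such events: "Adverse events will be monitored by the delivering midwife at each session using the standardised session log". Escalation of severe anxiety, acute distress or suicidal ideation starts from the same person: "the delivering midwife will immediately notify the principal investigator, discontinue participation, and refer the participant to specialist psychiatric services".

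The Data monitoring section (2.15) and the Ethics section (3) add no other route; both refer back to Harms.

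On the control arm, section 2.5.1 states: "Women in the control group will receive standard antenatal care as is typical in Poland". These women also get a booklet. They have no sessions, session log or delivering midwife.

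The fourth specific objective (1.2) reads: "To monitor and report any unintended adverse effects of the intervention, including temporary increases in emotional distress during or following sessions".

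On timing, section 2.8 states: "The intervention will be delivered between 24 and 34 weeks of gestation". Of Time II, section 2.12.2 says: "The second phase of data collection will consist solely of a follow-up measurement using the PRAQ-R2". Table 2 has no adverse-event row at any time point.

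**The concern.** The definition and the only stated tool both depend on a session taking place. This has two consequences.

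- **The count is one-sided.** The same distress in a control woman cannot enter the adverse-event record. The Discussion (4) accepts that anxiety at 34–37 weeks may fluctuate because birth is near, whatever the intervention does. A count from one arm cannot be set against that background. It may suggest harm if midwives record freely, or safety if they do not.
- **The stated tool ends before the definition does.** The definition and the fourth objective both cover distress that follows a session. After the final session there is no next session at which to record it.

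The trial has no data monitoring committee, and the article looks ahead to scale-up and policy use. Adverse events missed in the control arm cannot be recovered reliably afterwards, so the time to change this is before data collection.

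**Working it through.** The plan gives no figure on this point to reproduce. The check is mainly a comparison of passages, with some supporting arithmetic.

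**Coverage by arm**

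| Element | Intervention | Control |
|---|---|---|
| Adverse-event definition can apply (2.7) | yes | no, no sessions |
| Stated collection tool (2.7) | session log | none |
| Stated tool after the last session (2.7, 2.12.2, Table 2) | none | none |
| PRAQ-R2 at Time I and Time II | yes | yes |
| PHQ-4 at Time I and Time III; PPQ-II and Part B at Time III | yes | yes |
| Reasons for withdrawal and loss to follow-up (2.12.3) | yes | yes |

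So 1 of 2 arms, 37 of the 74 planned women, has a stated adverse-event route.

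**Time without a stated tool.** Inputs: enrolment at 24 to 30 weeks, sessions to 34 weeks at the latest, Time III at 6 or more weeks after birth (2.8). The documents give no expected week of birth, so 37 to 40 weeks is an assumption.

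- Gap after the last possible session = (birth week + 6) − 34. Birth at 37: 43 − 34 = 9 weeks. Birth at 40: 46 − 34 = 12 weeks.
- Largest share of follow-up that sessions can cover = (34 − enrolment week) / (birth week + 6 − enrolment week):
  - Enrolled at 24: 10/19 = 53% (birth at 37) or 10/22 = 45% (birth at 40).
  - Enrolled at 30: 4/13 = 31% or 4/16 = 25%.

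The gap is longer for a woman who finishes her sessions before 34 weeks.

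**What the logs can support.** Suppose all 37 intervention women are observed and every event reaches the log.

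- Chance of seeing at least one event = 1 − (1 − p)^37. For p = 5% this is 0.85; for p = 10% it is 0.98.
- With 0 events in 37, the one-sided 95% upper bound is 1 − 0.05^(1/37) = 7.8%.

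A within-arm description is therefore possible. A between-arm adverse-event rate is not, because the control arm has no numerator.

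**Two wording conflicts nearby**

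- Section 2.12.2 limits Time II to the PRAQ-R2. Sections 2.5.1 and 2.5.6 put further questions, on antenatal education and on other psychological support, at each follow-up or data-collection point.
- Section 2.7 speaks of ending participation after a severe event. Section 2.5.4 encourages women who stop the intervention to complete follow-up.

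**The case against.** These points can fairly be made for the plan:

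- **Both arms yield harm-relevant data.** PRAQ-R2, PHQ-4, PPQ-II and obstetric outcomes can show deterioration. A reader might infer that controls have no harms data at all; the documents do not support that. What controls lack is adverse-event data. The existing scores fill the gap only in part. PRAQ-R2 and PHQ-4 are planned as mean comparisons, which can hide a few women who get worse. PHQ-4 is not repeated until at least 6 weeks postpartum, which is late for temporary distress.
- **The objective is descriptive.** It promises to monitor and report, not to compare arms. A reader might infer that it cannot be answered. That goes too far: the logs capture events in a session and those reported at the next one.
- **Women who stop are not lost from view.** Reasons for non-attendance, discontinuation and withdrawal are recorded (2.5.5, 2.12.3), so distress as a reason for leaving can be seen.
- **There is contact and oversight outside sessions.** Research midwives keep in touch throughout, and the principal investigator reviews logs and receives reports within 24 hours. The contact is described for engagement and retention, with no adverse-event enquiry stated.
- **The Time II wording and Table 2 are not exhaustive**, as the questions in 2.5.1 and 2.5.6 show, and Part B is not itemised. A harms item there cannot be excluded, but none is stated.

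Two larger figures should also be resisted. Four weekly sessions from 24 weeks end at 27, which with birth at 40 gives (40 − 27) + 6 = 19 weeks; that combines the earliest start, the fastest stated interval between sessions, and the minimum number of sessions. An imbalance of about 4 events to 0 needs an assumed 10% background rate (0.10 × 37 = 3.7). The documents give no such rate; 5% would give 1.9 and 20% would give 7.4.

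That an article condenses a protocol does not answer the point. This one says that the full protocol and analysis plan are published within it, and 2.7 sets out a definite procedure.

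**Conclusion.** The point holds in a limited form. As written, section 2.7 gives an adverse-event count for one arm only, from a tool that ends with the sessions. The fourth objective can be met only descriptively and incompletely: events cannot be compared between arms or separated from background distress in late pregnancy, and delayed events can be missed.

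The stretch without a stated tool is at least about 9 to 12 weeks, on the assumption of birth at 37 to 40 weeks and the earliest Time III. The primary analysis is unaffected. This is a worthwhile and cheap design improvement.

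**What to change.** 1. In 2.7, define an adverse event for all randomised women from randomisation to Time III, without reference to a session.
2. Add the same short self-report harms item to the Time II and Time III LimeSurvey forms in both arms. Amend Table 2, and the restriction to the PRAQ-R2 in 2.12.2, which needs correcting anyway because of 2.5.1 and 2.5.6.
3. Keep the session log for immediate safety, and report its events separately, labelled as intervention arm only.
4. Tabulate by arm, from data already planned, the women whose PRAQ-R2 rose from Time I to Time II, and those below the PHQ-2 or GAD-2 cut-off (3 or more, section 2.6.2) at Time I and at or above it at Time III.
5. Reconcile the wording on ending participation in 2.7 with the encouragement of follow-up in 2.5.4.

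The cost is one short item on forms that every woman already receives, and one extra table. The drawbacks are slightly longer forms and recall error at Time III.

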#### Criteria for discontinuing or modifying the intervention

2.5.4

The intervention may be discontinued or modified for an individual participant in the following circumstances: withdrawal of informed consent at any point during the trial; emergence of a severe psychiatric condition requiring specialist treatment (e.g., acute psychosis, severe depressive episode); clinically significant deterioration in psychological wellbeing as assessed by the delivering midwife and confirmed by the principal investigator; initiation of pharmacological treatment for anxiety or depression during the trial period; obstetric complications requiring hospitalisation or precluding participation; preterm birth prior to completion of the intervention; or inability to continue participation due to unforeseen personal circumstances.

In cases of discontinuation, the participant will be referred to appropriate clinical or psychological services where indicated. All outcome data collected prior to discontinuation will be retained and included in the intention-to-treat analysis. Participants who discontinue the intervention but remain willing to complete follow-up assessments will be encouraged to do so.

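### The Harms section ends participation for severe anxiety or distress where other sections stop only the intervention; read literally, this could lose primary outcome scores in the intervention arm only

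*Protocol article*

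**What the plan says.** Harms (2.7) names three triggers (severe anxiety, acute distress, suicidal ideation) and says that in those cases "the delivering midwife will immediately notify the principal investigator, discontinue participation, and refer the participant to specialist psychiatric services". The same section defines an adverse event as "any unintended negative psychological or physical experience reported by a participant during or following a session" and gives the detection route: "Adverse events will be monitored by the delivering midwife at each session using the standardised session log".

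Section 2.5.4, which concerns stopping or modifying the intervention, lists among its grounds "clinically significant deterioration in psychological wellbeing as assessed by the delivering midwife and confirmed by the principal investigator". It then provides that "All outcome data collected prior to discontinuation will be retained and included in the intention-to-treat analysis" and that "Participants who discontinue the intervention but remain willing to complete follow-up assessments will be encouraged to do so". Section 2.12.3 repeats the encouragement to complete follow-up and keeps data from women who withdraw where that is possible.

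Under Control group (2.5.1), the comparison is standard antenatal care, and "women in the control group will receive an informational booklet on preparing for childbirth". No sessions, delivering midwife or session log are described for that arm.

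The Statistical analysis plan (2.14) makes the primary analysis an ANCOVA of the 34–37 week PRAQ-R2 on group and baseline score, using available outcome data. It assumes missing at random, adds a mixed model under the same assumption, plans no multiple imputation, and lists missing not at random as a limitation only.

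**The concern.** Two rules cover overlapping situations with different words. One ends *participation*; the other ends the *intervention* and still seeks follow-up. Staff reading 2.7 cannot tell whether the Time II questionnaire should still go to a woman stopped under it.

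The difference matters because the trigger is not neutral to the endpoint. Severe anxiety in a pregnant woman is likely to go with a high PRAQ-R2 score. Detection depends on the delivering midwife and the session log, so an equally distressed control woman would not be stopped by this route and would still contribute her score. If stopping includes outcome collection, loss of data depends on a post-baseline state and operates in one arm. Baseline adjustment does not recover a worsening that came after baseline.

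**Working it through.** **1. The wording side by side.**
- 2.7, first paragraph: clinically significant deterioration leads to referral, with a pointer to 2.5.4.
- 2.7, second paragraph: the three named states lead to the end of participation and referral. There is no pointer to 2.5.4 here and nothing on follow-up.
- 2.5.4 and 2.12.3: the intervention stops, and follow-up is encouraged.

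**2. What retained data can contribute.** Section 2.14 gives the primary outcome two prenatal measurements, baseline and post-intervention. For a woman stopped before 34 weeks, data collected beforehand means the baseline score. She drops out of the ANCOVA and adds essentially nothing about the treatment contrast to the mixed model. The PRAQ-R2 given at the last completed session (2.5.2, Table 1) does not fill the gap: it exists only in the intervention arm, only from Session 4 on, and is not among the measurements used in 2.14.

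**3. Size.** The article does not say how many women might be stopped, so there is no stated figure to reproduce. Inputs from 2.9: 37 women per arm, SD 8.56, planned difference 3.27. Everything else below is an assumption.

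*Raw means.* If k of 37 women are lost and their scores would have been D points above the mean of the others, the arm mean falls by k × D / 37.
- k = 2, D = 10: 20/37 = 0.54 points, or 0.54/3.27 = 17%.
- k = 3, D = 12: 36/37 = 0.97 points, or 0.97/3.27 = 30%.

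*Baseline-adjusted analysis.* The planned ANCOVA was simulated with no true effect, normal scores and 5,000 runs per cell. The k highest women were dropped from the intervention arm only, ranked either exactly on the final score or on the final score plus noise of 1 SD. The baseline–final correlation was 0.5 or 0.85. The article does not state it. The upper value is near what the planned size needs: without adjustment n = 2 × (8.56 × 2.80 / 3.27)² ≈ 108 per group, and 108 × (1 − ρ²) reaches the stated 31 only at ρ ≈ 0.84.

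Apparent effect in points (negative favours the intervention), with the two-sided rejection rate at a nominal 5%:

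| ρ | Removal | k = 1 | k = 2 | k = 3 | k = 4 |
|---|---|---|---|---|---|
| 0.5 | exact | −0.38 (6.3%) | −0.70 (7.1%) | −1.05 (10.8%) | −1.32 (13.1%) |
| 0.5 | noisy | −0.30 (6.1%) | −0.48 (6.2%) | −0.70 (6.9%) | −0.91 (8.3%) |
| 0.85 | exact | −0.15 (5.2%) | −0.27 (6.1%) | −0.40 (6.7%) | −0.55 (8.4%) |
| 0.85 | noisy | −0.12 (5.2%) | −0.19 (5.5%) | −0.29 (6.1%) | −0.35 (7.0%) |

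With k = 0 the bias is about 0 and rejection is 4.4% to 5.2%. Removing three women from both arms (ρ = 0.5, exact) gives a bias of −0.02, with 7.0% rejection. The bias therefore comes from the one-sidedness, although not all of the excess rejection does.

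For k = 3 the range is 0.29 to 1.05 points, that is 0.29/3.27 = 9% to 1.05/3.27 = 32% of the planned difference.

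**The case against.** The strongest reply is that the harmful reading is not the natural one. Section 2.7 itself points to 2.5.4 for deterioration. Section 2.5.4 uses the word participation when listing reasons to stop the intervention. The delivering midwife has no role in collecting outcomes, because questionnaire links go straight to participants (2.12). Read together, the sections can mean that sessions stop and outcomes are still sought. This stands as a plausible reading, but it does not settle the matter: the paragraph with the three triggers uses the wider word and is silent on follow-up.

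A reader might infer that severe anxiety is the primary outcome itself, so that the worst outcomes are certain to be removed from one arm. The document does not support that. Severe anxiety is tied to no PRAQ-R2 value, acute distress and suicidal ideation are not the primary outcome, and a woman stopped mid-programme need not have one of the highest scores at 34–37 weeks. Women in either arm can also be lost for other reasons; only this trigger is one-sided.

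A reader might also infer that objective 4 fails without a control rate of distress. As written in 1.2, it is descriptive and concerns effects of the intervention around sessions. It promises no comparison between arms.

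Finally, research midwives keep in touch with participants throughout the study (2.12.3), so control women are not without contact. That contact is described for retention, with no adverse event or stopping role. The article also anticipates no serious adverse events, so the number affected may be 0 or 1. That limits the expected size but does not remove the conflict.

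**Conclusion.** The contradiction between 2.7 and sections 2.5.4 and 2.12.3 is real and should be resolved. Bias in the primary comparison is conditional on participation being taken to include outcome collection and on at least one woman being stopped. Under those conditions it favours the intervention, and the planned analyses would not correct it.

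The size cannot be fixed from the document. Three women lost would give about 0.3 to 1.05 points; one would give about 0.1 to 0.4. These figures rest on the assumed numbers lost, correlations, normal scores and closeness of the trigger to the final score. They also ignore the narrowing of baseline scores by the entry threshold of 30. The wording conflict is certain; the size of its effect is not.

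**What to change.** Reconcile 2.7 with 2.5.4 and 2.12.3 so that two matters are kept apart: the clinical decision on sessions and referral, which is the sponsor's and on which no view is given here, and outcome collection. State, consistently with 2.5.4 and 2.12.3, whether the Time II and Time III questionnaires are still sought from women who are willing. This should be settled before the first such event, because a score not collected at 34–37 weeks cannot be recovered.

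In 2.14, commit to reporting these discontinuations by arm and reason, and add one simple sensitivity analysis under missing not at random for missing Time II scores, for example a delta adjustment over a stated range.

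The cost is a few sentences, a little more analysis, and online questionnaires sent to a few distressed women who may decline. A table of harms by arm from the PRAQ-R2 and PHQ-4, both already collected in both arms, would be a useful option; objective 4 as written does not require it.

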### Participant timeline

2.8

The schedule of enrolment, interventions, and assessments is presented in Figure 1 and Table 2. Eligible participants will be enrolled and randomised between 24 and 30 weeks of gestation (Time I). The intervention will be delivered between 24 and 34 weeks of gestation. The primary outcome assessment will be conducted at 34–37 weeks of gestation (Time II). The postpartum assessment will be conducted at six or more weeks after delivery (Time III). The duration of recruitment will continue until the target sample size of 37 participants per group is achieved.

